## Abstract

**Background:**

There is increasing evidence supporting the use of faecal immunochemical tests (FIT) in patients reporting symptoms associated with colorectal cancer (CRC), but most studies until now have focused on selected subjects already referred for investigation. We therefore set out to determine the accuracy and predictive values of FIT in a primary care population.

**Method:**

A prospective, multicentre, single-gated comparative diagnostic study on quantitative FIT in patients aged 40 years and above presenting in primary care with symptoms associated with CRC will be conducted. Patients representing the whole spectrum of severity of such symptoms met with in primary care will be eligible and identified by GPs.

Participants will answer a short form on symptoms during the last month. They will provide two faecal samples from two separate days. Analyses will be performed within 5 days (QuikRead go®, Aidian Oy). The analytical working range is 10–200 μg Hb/g faeces.

Reference test will be linked to the Swedish Colorectal Cancer Registry up to 2 years after inclusion. Accuracy, area under ROC curves, and predictive values will be calculated for one FIT compared to the highest value of two FIT and at cutoff < 10, 10–14.9, 15–19.9 and ≥ 20 μg Hb/g faeces. Subgroup analyses will be conducted for patients with anaemia and those reporting rectal bleeding. A model-based cost-effectiveness analysis based on the clinical accuracy study will be performed.

Based on previous literature, we hypothesized that the sensitivity of the highest value of two FIT at cutoff 10 μg Hb/g faeces will be 95% (95% CI + / − 15%). The prevalence of CRC in the study population was estimated to be 2%, and the rate of non-responders to be 1/6. In all, 3000 patients will be invited at 30 primary care centres.

**Discussion:**

This study will generate important clinical real-life structured data on accuracy and predictive values of FIT in the most critical population for work-up of CRC, i.e. patients presenting with at times ambiguous symptoms in primary care. It will help establish the role of FIT in this large group.

**Trial registration:**

NCT05156307. Registered on 14 December 2021—retrospectively registered.

## Background

Globally, colorectal cancer (CRC) was the third most common type of cancer in 2020 with 1.9 million new cases, and more than 900,000 deaths, second only to lung cancer [1]. Screening programs are operating in many countries, but participation varies widely and most patients are diagnosed via the clinical route [2]. Symptoms associated with CRC are non-specific and predictive values are generally low [3]. Clinical decision-making for referral is often challenging, e.g. for elderly frail patients who are at an increased risk of CRC but also report bowel symptoms more frequently. Colonoscopy for work-up is costly and requires extensive bowel preparation. The demand is ever-increasing and long waiting times are commonplace.

In this situation, faecal immunochemical tests (FIT) have received increasing attention as an adjunct to the clinical management of patients presenting with symptoms associated with CRC. A systematic review and meta-analysis, based on 10 primary studies, reported FIT to be associated with very high negative predictive values (NPVs) that may correctly rule out CRC and indicated that colonoscopy could be avoided in 75–80% of symptomatic patients [4]. Sensitivity at cutoff 10 μg Hb/g faeces of several FIT for CRC (OC-Sensor, HM-JACKarc, and QuikRead go) has been reported in the range of 92–100% [4–6]. FIT alone, or within a prediction model, is found to be more reliable than merely symptom-based criteria for investigation [7]. But, importantly, almost all of the previous studies have been conducted amongst patients already referred for colonoscopy. Consequently, the results do not apply to a low-risk primary care population where most patients present [8].

However, lately a few studies have been published on the use of FIT in primary care from countries where FIT has already been introduced as a part of the workup of lower gastrointestinal symptoms [9–12]. As such, these studies have focused on patients with non-alarm symptoms, who are not to be referred urgently. But it is well known that the severity of any symptom may be interpreted differently amongst GPs [13], and as follows, the included population may differ between clinical settings and local medical traditions etc. There is a lack of prospective diagnostic studies on FIT in primary care populations that are not restricted to certain symptoms or groups. The crucial question on whether FIT is to be used as a rule-in or rule-out test also remains unresolved [12].

Rectal bleeding is generally considered an alarming symptom of CRC, but it could be very difficult to assess the severity of this symptom from a patient’s history. It is therefore interesting that at least two recent studies found that FIT may identify patients at an increased risk for CRC, even amongst those reporting rectal bleeding [6, 14]. Given the commonness of rectal bleeding, this is an important reason for further investigation of the performance of FIT.

Anaemia is another common first symptom of CRC, and in a screening context, it is associated with a lower sensitivity of FIT [15]. For this reason, it is possible that FIT should not be used in symptomatic patients with anaemia, in order to avoid false-negative outcomes. This is a key aspect of a potential use of FIT amongst symptomatic patients as approximately some 40% of CRC patients overall are expected to be anaemic at the time of diagnosis [16, 17]. Thorough knowledge on the accuracy of FIT, specifically in patients with either anaemia or amongst those who report rectal bleeding, is a decisive aspect on the potential use of FIT in symptomatic patients, in particular for symptomatic patients presenting in primary care.

The use of FIT has likely been found to be a cost-effective strategy for triaging patients who present with lower abdominal symptoms to colonoscopy [5], but again, this analysis was based on studies carried out on patients already referred for colonoscopy, and only one study evaluating FIT in primary care. Further diagnostic accuracy studies based on symptomatic primary care populations are therefore warranted in order to enable updated health economic analyses.

## Methods

### Aim

The aim of this study is to determine the accuracy and predictive values for colorectal cancer of a quantitative FIT in patients presenting in primary care with symptoms associated with colorectal cancer.

### Design

This is a prospective, multicentre, single-gated comparative diagnostic accuracy study of a quantitative FIT in primary care, Sweden, and will be carried out according to the STARD guidelines [18]. Reference test will be linked to a cancer registry at the latest 2 years after the FIT analysis.

### Study setting and participants

This will be a nationwide study, and patients will be invited at primary health care centres located in sparsely populated northern parts, as well as in larger city centres in central Sweden. The catchment population of each primary care centre will vary. The majority of them will be part of public healthcare, but some will be privately managed centres.

Patients from the age of 40 years and above who present in primary care with symptoms possibly associated with CRC are eligible. They must understand Swedish well enough to comply with the study instructions. Any comorbidity, previous history or medication is no hindrance for participation. Anti-coagulation or NSAIDs do not affect the outcome of FIT and patients receiving such treatment can be included [19]. Asymptomatic patients referred for bowel investigation for other reasons (e.g. heredity) are not eligible.

### Participant identification and consent

Participants will be identified by physicians at the participating centres while listening to the history and symptoms reported by patients. Symptoms for study purposes will not be pre-specified, and it will be up to each GP to decide whether the symptoms reported by patients could be associated with CRC, to resemble the real conditions in primary care. The only restriction will be that CRC at some point during the consultation must be considered one of many possible differential diagnoses.

Physicians at participating centres will be encouraged to invite patients from the whole spectrum of severity of symptoms. There will be no specific claims related to the severity of symptoms but a bottom-line is that they must trigger a medical response of any kind. This involves possible alternatives ranging from expectancy and clinical follow-up only (e.g. discussing bowel habits again), to blood tests only (e.g. merely B-haemoglobin), routine faecal haemoglobin tests, rectoscopy only, or routine or urgent referral for complete bowel examination [20].

There will be no specific requirements on the qualifications of physicians identifying eligible patients for the study. It may involve experienced specialists in primary care as well as junior doctors, as this also resembles the real conditions in primary care.

Physicians will briefly inform and invite eligible patients to participate in the study at the consultation. Patients who are interested in participating in the study will be provided with a “study package” and a nurse assistant will demonstrate the content in detail. Patients will bring the study package back home, and if they finally decide to participate in the study, they will sign an enclosed written consent form and enclose this together with their first faecal sample. Patients will be thus identified and invited consecutively at each primary care centre, but they will not be considered included in the study until a signed written informed consent has arrived in the laboratory. First patients, to test study logistics, were included in May 2021.

### Collection of clinical data

In the study package, patients will find a thorough study information and detailed written and pictorial instructions for the collection of faecal samples. In addition, there are two sample collection tubes, two faecal catchers to simplify the sample collection, two transportation tubes, two padded stamped envelopes and two specific referral forms. Patients will provide faecal samples from two separate days. They will be instructed to provide the samples as soon as possible. Patients will send the sample on the same day as a collection or keep it in the fridge overnight. At a few sites, the patients will drop off the samples at the primary health care centre instead of sending them by ordinary mail. Patients are instructed to fill in the date of collection of each sample on the referral forms.

The study package also holds a short questionnaire on the presence of symptoms during the last 4 weeks. The symptoms asked for are rectal bleeding, passage of rectal mucus, abdominal pain, weight loss, and change of bowel habits (more often/seldom and looser/harder). Finally, there is one question on further investigation or clinical follow-up (alternatives as outlined above). Patients will answer these questions at home and enclose the questionnaire with the first sample.

All materials to be returned are identified with serial study numbers. Before leaving the primary care centre with the study package, a nurse assistant will paste a barcode label with a personal ID number on both referral forms. The nurse assistant will also log the date, serial number, age and sex of all patients receiving a study package. The collected data, from all participating centres, will constitute the basic study population and compliance will be calculated using this data as the denominator. The nurse assistant will also make sure there is a recent analysis of B-Hb, within 2 weeks at the most, for each potential study participant.

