### FIT analysis

Incoming samples will be analyzed on a daily basis, except for weekends, at three larger laboratories. One is a university clinical research laboratory; and the other two are hospital laboratories accredited according to ISO 17025 and ISO 15189, respectively. Samples will be analyzed within 5 days and kept at room temperature since the collection. The analysis will be performed using the QuikRead go® instrument (Aidian Oy) according to a Standard operating protocol (SOP) from the manufacturer. Laboratory staff will receive specific training for this purpose. A very limited number of laboratory technicians at each laboratory will be involved. Calibrations of the instrument will be carried out every week using QuikRead FOB Positive Controls.

QuikRead go® is a point-of-care FIT system that demonstrated accurate analytical performance in a recent evaluation [21]. The analytical working range of QuikRead go® is 10–200 μg Hb/g faeces (50–1000 ng/ml). Concentrations above this are displayed as > 200 μg/g, and concentrations below are displayed as < 10 μg Hb/g faeces. Accuracy will be calculated for one and two FIT and at cutoff < 10, 10–14.9, 15–19.9 and ≥ 20 μg Hb/g faeces, respectively.

The outcome of the study FIT will not be reported to participating centres. If requested for clinical purposes, physicians will have to order any FIT according to local routines.

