### Reference test

The Swedish Colorectal Cancer Registry (SCRCR) is a nationwide registry for CRC with, in practice, complete coverage [22]. Benefitting from the use of personal ID numbers, study participants will be linked to this register at the latest 2 years after the date of the FIT analysis and this will serve as a reference test. In this way, we expect all patients with CRC (ICD-10 C 18–20) will be identified. Date of diagnosis of CRC will be retrieved from SCRCR, and the time period from the date of faecal sample collection until diagnosis will be calculated. Subsite (caecum, ascendens, transversum, descendens, sigmoid and rectum) and TNM stage will be requested. Patients with no CRC registered in the SCRCR within 2 years after FIT analysis will be categorized as “no CRC”. The linkage to SCRCR will also involve data on vital status (including date of death).

A new unknown proportion of patients included in the study will be referred for colonoscopy as part of the clinical workup of their symptoms. For these patients, data from colonoscopy reports will be retrieved to give an account of diagnoses with FIT concentrations below the various chosen thresholds and also to inform the health economic evaluation. Date of investigation, completeness, quality of bowel cleansing, and findings will be extracted. This will include both macroscopic and microscopic findings and be categorized as CRC, advanced adenoma, non-advanced adenoma, inflammatory bowel disease, diverticulosis/diverticulitis, angiodysplasia, and no abnormalities.

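### No rule keeps the FIT sample ahead of colonoscopy or CRC diagnosis, and the start of the CRC window is not fixed

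*Protocol article*

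**What the plan says.** **Sampling.** Under Collection of clinical data, patients take the package home and sample on two separate days. The timing rule is "They will be instructed to provide the samples as soon as possible". No latest date is set, and there is no link to bowel preparation, colonoscopy or diagnosis. Dates are captured: "Patients are instructed to fill in the date of collection of each sample on the referral forms". The handout date is logged at the centre.

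**Parallel work-up and inclusion.** Under Participant identification and consent, the clinical response may extend to "routine or urgent referral for complete bowel examination". Patients decide at home whether to take part, and "they will not be considered included in the study until a signed written informed consent has arrived in the laboratory". The consent travels with the first sample.

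**Classification.** The Reference test section states: "Patients with no CRC registered in the SCRCR within 2 years after FIT analysis will be categorized as" free of CRC. The same section describes registry linkage no later than two years after FIT analysis, expects every CRC patient to be found, and retrieves the dates of diagnosis and colonoscopy. It also calculates the interval from sample collection to diagnosis. None of these dates is used to order, exclude or classify. The abstract uses another reference point: "Reference test will be linked to the Swedish Colorectal Cancer Registry up to 2 years after inclusion".

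**Eligibility.** Under Study setting and participants, previous history is no bar to entry.

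**The concern.** In a diagnostic accuracy study the index test should describe the patient before the reference investigation has altered the bowel or removed the lesion. Here the interval from handout to sampling has no upper limit, and the patients investigated fastest are plausibly those in whom CRC is most frequent. A sample collected after biopsy, polypectomy or tumour removal would enter the estimate like any other. The hypothesis rests on the higher of two values, so a late second sample matters too.

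The window raises a related question. If a patient is diagnosed after handout but before the sample is analysed, the classification sentence does not clearly count that cancer. With no start date at all, an old CRC could count as a case, since earlier disease does not exclude. Either way the decision would be made after the data are seen, in a sensitivity estimate resting on about 50 cancers.

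**Working it through.** **1. The plan's own figures (Sample size section).** Inputs: sensitivity 95%, lowest acceptable limit 80%, two-sided alpha 0.05, power 80%, prevalence 2%, non-return 1/6.

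- Score formula: n = [(1.96·√(0.80·0.20) + 0.842·√(0.95·0.05)) / 0.15]² = 41.6.
- With continuity correction: n = (41.6/4)·[1 + √(1 + 2/(41.6·0.15))]² = 48.03, in line with the stated 48.
- 48/0.02 = 2400, so 2352 without CRC. 50/0.02 = 2500. 2500/(1 − 1/6) = 3000.

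These figures reproduce, and this point contests none of them. The second method behind the figure of 50 cannot be rebuilt from the article.

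**2. Margin at 50 CRC cases.** Exact (Clopper-Pearson) lower 95% limits: 46/50 gives 80.8% and 45/50 gives 78.2%. At most four false negatives are compatible with the 80% bound. If true sensitivity is 95%, P(at least 46 of 50 positive) = 0.896. Each case is worth 1/50 = 2 percentage points.

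**3. Order of events as written.** Handout → (no stated limit) → sample collected → consent and sample reach the laboratory, which is inclusion → analysis. On the last step the FIT analysis section says "Samples will be analyzed within 5 days and kept at room temperature since the collection". Colonoscopy and diagnosis can fall anywhere along this line. The open-ended step is handout to collection; the later steps are days apart. There are also up to two FIT analyses per patient, and the classification sentence does not say which one it means.

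**4. Size, under assumptions.** The documents give neither the share of CRC cases sampled late nor the FIT sensitivity in such samples. Assume an expected 1, 3 or 5 of 50 (2%, 6%, 10%).

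*(a) The case is kept as CRC with a distorted FIT.* Expected sensitivity = 0.95·(1 − f) + s·f, where f is the late share and s the sensitivity in late samples. The probability of meeting the bound is P(at least 46 of 50) at that sensitivity.

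| Expected late cases | Sensitivity, s = 0 to 0.5 | P(lower limit ≥ 80%) |
|---|---|---|
| 0 | 95.0% | 0.90 |
| 1 | 93.1–94.1% | 0.74–0.83 |
| 3 | 89.3–92.3% | 0.37–0.66 |
| 5 | 85.5–90.5% | 0.13–0.48 |

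With s = 0.75 the probabilities are 0.87, 0.80 and 0.73. If late sampling instead made every such FIT positive (s = 1), expected sensitivity would rise only to 95.1%, 95.3% or 95.5%.

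*(b) The case is classed as free of CRC.* Losing 1, 3 or 5 leaves 49, 47 or 45 cancers, and the probability of meeting the bound is 0.90, 0.79 or 0.81. It is not monotone because the exact limit moves in steps. Specificity, if all five are FIT-positive: 0.70·2450/(2450 + 5) = 1715/2455 = 69.9%, against 70.0%.

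One case can follow route (a) or route (b), not both.

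**The case against.** The strongest reply is that much of this is detail an article may leave to a fuller document. Patients are told to sample promptly, the written instructions in the package are not shown, and every date needed to spot a late sample is recorded. Excluding post-procedure samples could sit in an analysis plan. The reference points are also close together for the first sample, since consent comes with it and analysis follows within days.

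A reader might go further and infer that the plan opens the CRC window only at FIT analysis and labels every earlier cancer as disease-free. The documents do not support that. The abstract, the Design section and the linkage sentence give outer limits, not start dates. The classification sentence speaks of registration, which can follow diagnosis. The same section expects all CRC patients to be identified. The mislabelling is a possible result of loose wording, not a stated rule. Nor can both harms be added for one case, and falling below 48 cancers is no cliff: exact power is 0.909 at 48 and still 0.81 at 45.

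These limits on the window argument stand. The reply on sampling order stands only in part. The article does not merely stay silent: it states an inclusion rule that admits anyone whose consent and sample arrive, and a classification rule with a time reference. Together they let wrongly ordered samples in and leave an earlier CRC without defined handling.

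**Conclusion.** The point holds in a limited form. Followed as written, the plan counts samples collected after colonoscopy or CRC diagnosis. It also does not fix where the CRC window starts: the classification sentence, taken literally, leaves out a cancer diagnosed between handout and analysis, and the abstract counts from inclusion instead.

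The frequency is unknown and may be small; 1 to 5 of 50 is an assumption, as is the sensitivity in late samples. The effect on specificity is negligible. What makes the point worth acting on is the narrow margin on sensitivity, where one result separates 46/50 from 45/50 at the 80% bound, together with a cheap repair. It should be settled before the registry linkage.

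**What to change.** Add to the Reference test and Statistical analysis sections:

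- **Window.** It runs from the logged date of study-package handout to 2 years after the first FIT analysis. A new CRC diagnosed from the handout date counts as CRC; a CRC diagnosed before that date is not a study case. Align the abstract with this.
- **Samples.** The main accuracy analysis uses only samples collected before the first colonoscopy or CRC diagnosis. One FIT is compared with the highest of two in patients whose two samples both qualify.
- **Reporting.** Give the number excluded, and repeat the analysis with all samples as a sensitivity analysis.

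**Cost.** A few sentences. Handout, collection, colonoscopy and diagnosis dates are already collected, and no sample-size figure changes. The downside is that a few late samples, possibly from CRC patients, leave the main analysis, and the comparison of one with two FIT rests on somewhat fewer patients. The all-samples analysis shows how much that matters.

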### Statistical analysis

A few subanalyses are planned from the outset. Patients will be categorized according to WHO definition and Hb concentration < 120 g/L for women and < 130 g/L for men will be considered as anaemia [26]. We will estimate accuracy and predictive values for patients with anaemia vs normal haemoglobin and expect the sensitivity of FIT for CRC to be lower in patients with anaemia. We will also estimate accuracy and predictive values for patients reporting rectal bleeding vs those who do not report rectal bleeding. We expect sensitivity to be higher amongst patients reporting rectal bleeding.

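### The rectal-bleeding subgroup is defined by a home questionnaire returned with the first FIT sample, so membership can be influenced by blood first seen in that sample

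*Protocol article*

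**What the plan says.** Under Participant identification and consent, the protocol article has physicians identify patients from the symptoms they describe at the consultation. Under Collection of clinical data it then sets out what is recorded.

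- At the centre: "The nurse assistant will also log the date, serial number, age and sex of all patients receiving a study package". No symptom is on that list.
- In the package: "The study package also holds a short questionnaire on the presence of symptoms during the last 4 weeks". On content: "The symptoms asked for are rectal bleeding, passage of rectal mucus, abdominal pain, weight loss, and change of bowel habits".
- Completion and return: "Patients will answer these questions at home and enclose the questionnaire with the first sample".
- Timing of sampling: "They will be instructed to provide the samples as soon as possible". No maximum interval is given, but patients write each collection date on the referral forms.

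The Statistical analysis section states: "We will also estimate accuracy and predictive values for patients reporting rectal bleeding vs those who do not report rectal bleeding". It expects higher sensitivity in those reporting bleeding. The Health economic evaluation section plans ICERs for the same subgroup. The Background says that knowledge of accuracy in patients with anaemia or "amongst those who report rectal bleeding, is a decisive aspect on the potential use of FIT".

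**The concern.** A physician deciding whether to rely on FIT knows only what the patient has reported up to that moment. A subgroup result that supports this decision should use bleeding status fixed before the index sample exists. Here the status comes from a form that travels with the first sample, and the order of form and sample is left open.

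The package includes faecal catchers, so patients handle and see the stool. Someone who first notices blood that day answers yes correctly, because the day lies within the 4 weeks. The same blood is in the material sent for FIT. Membership of the bleeding group can then depend on the index test material. In the other direction, a patient who consulted about bleeding and returned the form late could correctly answer no.

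The first mechanism moves FIT-positive patients into the bleeding group. Among patients without CRC this lowers specificity there and raises it in the comparison group. Among patients with CRC it raises sensitivity there and lowers it in the comparison group, which is the contrast the plan expects. Predictive values and subgroup ICERs inherit the shift. The anaemia subgroup does not share the problem, because it rests on a blood test that is independent of the stool sample.

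**Working it through.** The plan gives no figure for this bias, so there is none to reproduce. The calculation shows what the mechanism could do if FIT performed identically in both groups.

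**Inputs from the Sample size section.** 50 CRC cases at 2% prevalence: 50/0.02 = 2500 included, so 2500 − 50 = 2450 without CRC. Sensitivity 95%, accepted specificity 70%.

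**Assumptions not in the document.** The share with bleeding before sampling, and the share of the others who first see blood at collection, answer yes and are FIT-positive.

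**Specificity, 30% bleeding before sampling.** Bleeding 0.30 × 2450 = 735, of whom 0.70 × 735 = 514.5 are FIT-negative. Others 1715, of whom 1200.5 are FIT-negative and 514.5 FIT-positive. If a fraction s of the others switches, all FIT-positive, observed specificity is 514.5/(735 + 1715s) against 1200.5/(1715 − 1715s).

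| s | Patients moved | Bleeding | No bleeding | Gap (points) | Moved, as share of the 514.5 FIT-positive others |
|---|---|---|---|---|---|
| 2% | 34.3 | 514.5/769.3 = 66.9% | 1200.5/1680.7 = 71.4% | 4.5 | 6.7% |
| 5% | 85.75 | 514.5/820.75 = 62.7% | 1200.5/1629.25 = 73.7% | 11.0 | 16.7% |
| 10% | 171.5 | 514.5/906.5 = 56.8% | 1200.5/1543.5 = 77.8% | 21.0 | 33.3% |

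**Sensitivity, 40% of CRC cases bleeding before sampling, 10% of the rest switching.** Bleeding 20 (19 FIT-positive), others 30 (28.5 FIT-positive), 3 move. Observed: 22/23 = 95.7% against 25.5/27 = 94.4%, a gap of 1.2 points before rounding. At 2% switching (0.6 cases): 19.6/20.6 = 95.1% against 27.9/29.4 = 94.9%, about 0.25 points.

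**The same mechanism, expressed per FIT-positive patient.** Let b be the share bleeding before sampling, f the share of FIT-positive others who switch, and p the probability of a positive FIT (0.95 with CRC, 0.30 without). The observed positive rate is [bp + (1−b)pf]/[b + (1−b)pf] in the bleeding group and p(1−f)/(1−pf) in the other.

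| b | f | Sensitivity gap (points) | False-positive-rate gap (points) |
|---|---|---|---|
| 0.5 | 0.05 | 0.5 | 2.1 |
| 0.3 | 0.10 | 1.4 | 6.7 |
| 0.2 | 0.20 | 3.3 | 18.0 |

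The first and last rows are the extremes over b from 0.2 to 0.5 and f from 0.05 to 0.20.

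**Against sampling error.** The standard error of the sensitivity difference with 23 and 27 cases is √(0.957×0.043/23 + 0.944×0.056/27) ≈ 6.1 points, so a 1-point artefact would not be noticeable. For specificity with 735 and 1715 patients it is √(0.21/735 + 0.21/1715) ≈ 2.0 points, so an artefact of 4.5 points could be read as a real difference.

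**The case against.** Several points on the other side stand.

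- **The 4-week window.** A reader might infer that the form captures the sampling day instead of the complaint heard by the physician. The text does not support that. With samples requested promptly, 4 weeks will usually cover the visit and a period before it.
- **Self-report is the declared construct.** The Abstract and the Statistical analysis section define the subgroup by what patients report. The article notes that physicians interpret symptom severity differently, so a standard patient form is a defensible choice. The issue is its timing and link to the sample.
- **The artefact is possible, not shown.** A reader might infer that the contrasts are in part created by the index sample. The article gives no evidence of this. The form travels with the first sample, so it is answered before that sample's FIT result exists. Some association between visible blood and a positive FIT is genuine. The illustrations assume no true difference and make every switcher FIT-positive.
- **The larger gaps need extreme inputs.** The 11- and 21-point gaps require about 17% and 33% of FIT-positive patients without earlier bleeding to see blood first on the sampling day.
- **Late return can be examined.** The package date and collection dates are recorded, so visit-to-sample delay can be calculated.
- **The article is condensed.** Form instructions may sit in study documents that are not shown, so one cannot say that consultation symptoms are recorded nowhere, only that no such record is described.

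These points limit the size and certainty of the concern. They do not remove it: as described, the only source for the subgroup is returned with the index sample, and nothing places it before collection.

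**Conclusion.** The concern holds as a weakness in a secondary analysis. On the article's description, bleeding status is not fixed before the index sample, so it can be influenced by blood first seen in that sample and may differ from what was reported at the visit. Any such bias lowers specificity and slightly raises sensitivity in the bleeding group relative to the other, the latter in the expected direction.

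Its size cannot be derived from the document. Under the assumptions shown it is about 1 point for sensitivity (0.5 to 3.3 across the per-FIT-positive scenarios). It could be several points for specificity, which matters more because false positives drive FIT-triggered colonoscopies and hence the subgroup ICERs. The documents do not show that the bias occurs. The primary accuracy results and the sample size are unaffected. The point merits action because the subgroup is treated as decisive and the remedy is nearly free.

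**What to change.** Establish bleeding status before the index sample, in one of two ways.

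1. Preferred: add a yes/no item on rectal bleeding reported at this consultation to the referral form that is labelled before the patient leaves, filled in by or on the word of the physician who took the history.
2. At minimum: instruct patients to complete and date the questionnaire before the first stool collection.

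Define the bleeding subgroup in the Statistical analysis and Health economic evaluation sections by that pre-sample status. Under option 1, keep the 4-week questionnaire answer as a sensitivity analysis.

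The cost is one item on an existing form, or one instruction and a date field. The consultation item would reach the study only for patients who return a signed consent, as with the rest of the package. The downside is that inclusion began in May 2021 and participants already included lack the pre-sample record. Analyse them by the existing questionnaire, report them separately so that two definitions are not mixed in one estimate, and use the recorded package and collection dates to check for long visit-to-sample delays.
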